## Abstract

**Background:** Pancreatic fistula (PF), i. e., a failure of the pancreatic anastomosis or closure of the remnant pancreas after distal pancreatectomy, is one of the most feared complications after pancreatic surgery. PF is also one of the most common complications after pancreatic surgery, occurring in about 30% of patients. Prevention of a PF is still a major challenge for surgeons, and various technical and pharmacological interventions have been investigated, with conflicting results. Pancreatic exocrine secretion has been proposed as one of the mechanisms by which PF occurs. Pharmacological prevention using somatostatin or its analogs to inhibit pancreatic exocrine secretion has shown promising results. We can hypothesize that continuous intravenous infusion of somatostatin-14, the natural peptide hormone, associated with 10–50 times stronger affinity with all somatostatin receptor compared with somatostatin analogs, will be associated with an improved PF prevention.

**Methods:** A French comparative randomized open multicentric study comparing somatostatin vs. octreotide in adult patients undergoing pancreaticoduodenectomy (PD) or distal pancreatectomy with or without splenectomy. Patients with neoadjuvant radiation therapy and/or neoadjuvant chemotherapy within 4 weeks before surgery are excluded from the study. The main objective of this study is to compare 90-day grade B or C postoperative PF as defined by the last ISGPF (International Study Group on Pancreatic Fistula) classification between patients who receive perioperative somatostatin and octreotide. In addition, we analyze overall length of stay, readmission rate, cost-effectiveness, and postoperative quality of life after pancreatic surgery in patients undergoing PD.

**Conclusion:** The PreFiPS study aims to evaluate somatostatin vs. octreotide for the prevention of postoperative PF.

## Introduction

Although the mortality following pancreatic resection has decreased over the last decades, the morbidity of these procedures is still significant. Pancreatic fistula (PF), also named pancreatic leak, is one of the main causes of morbidity after pancreatic surgery [both pancreaticoduodenectomy (PD) or distal pancreatectomy (DP)] [(1) #1158] [(2) #1159] [(3) #1160] [(4) #1161] [(5) #1162]. PF can be associated with a reoperation, intensive care unit admission or death, and its management often required extended hospital stay or readmission, numerous serial CT scans, and image-guided procedures. The physical and emotional burden these complications place upon patients, as well as the financial cost to the healthcare system, cannot be overestimated. Currently, despite numerous trials and research, no preoperative or intraoperative techniques have worldwide imposed its ability to decrease the risk of these complications.

Because pancreatic exocrine secretion has been proposed as the mechanism by which pancreatic complications occur, the inhibition of this secretion has been evaluated as a method to reduce the risk of PF. Several prospective randomized trials [(6) #1164] [(7) #1165] [(8) #1166] [(9) #1167] [(10) #1168] [(11) #1169] of perioperative octreotide have suggested a benefit on PF rate, however with conflicting results between European and North American trails. The prophylactic role of octreotide on PF, the only drug with authorization to use in Europe, is still debated even if it is recommended for routine use in patients undergoing pancreatic surgery by the Cochrane [(12) #1170].

Nevertheless, Allen et al. recently published a randomized, double-blind, placebo-controlled phase III trial comparing SOM230 vs. placebo in patients undergoing PD or DP [(13) #1171]. Interestingly, testing this new somatostatin analog, associated with a stronger affinity for four of five subtypes of somatostatin receptor, they showed a 56% significant relative risk reduction in postoperative PF.

In view of this impressive result, we can hypothesize that improved pharmacodynamics and higher affinity for somatostatin receptor lead to stronger pancreatic exocrine secretion inhibition and better PF prevention. Consequently, continuous intravenous infusion of somatostatin-14, the natural peptide hormone, associated with 10**–**50 times stronger affinity with all somatostatin receptors, could be associated with an improved PF prevention.

Thus, the aim of this study is to assess continuous intravenous infusion of somatostatin-14 that has a high binding affinity profile for all of the five somatostatin receptors in a prospective randomized controlled trial. The primary endpoint of this trial will be to compare 90-day ≥grade B or C postoperative PF as defined by the International Study Group on Pancreatic Fistula (ISGPF) classification (Figure 1) between patients who receive perioperative somatostatin or octreotide.

**Figure 1 F1:**
[figure not shown]
Pancreatic fistula defined by ISGPF classification.

## Methods/Analysis

### Study Organization and Coordination

PreFiPS is designed and coordinated by [name] (M.D., Ph.D.). PreFiPS is conducted as a randomized, prospective multicenter study involving the participation of the FRENCH (*Fédération de Recherche en Chirurgie*) network. The coordinating center is represented by Cochin Hospital—Paris Descartes University (Paris, France). The investigators intend to include 16 participating centers. The study receives funding from APHP (Assistance-Publique-Hôpitaux de Paris) and by delegation: Clinical Research and Innovation Delegation (DRCI).

### Study Objectives

The main objective of this study is to compare 90-day ≥grade B or C postoperative pancreatic fistula as defined by the last ISGPF classification between patients who receive perioperative somatostatin and octreotide.

Secondary objectives include the following endpoints between patients who receive perioperative somatostatin and octreotide:

60-day grade 3 pancreatic complication rates (fistula, leak, and abscess) as defined by the Memorial Sloan Kettering Cancer Center surgical secondary events system (Table 1).90-day overall PF rate (grades A, B, and C) as defined by the previous ISGPF classification.90-day overall PF rate (grades B and C) as defined by the last ISGPF classification.90-day overall complication rate (grades 1–5), severe complication rate (grades 3–5), and mortality (grade 5) according to Dindo–Clavien classification [(14) #398] (Table 2).Overall length of drainage required in patients who develop pancreatic complications—overall length of stay and readmission rate.Cost-effectiveness.Postoperative quality of life after pancreatic surgery (only in patients undergoing PD).

**Table 1 T1:** Memorial sloan kettering cancer surgical secondary events database classifications.

**Grade**	**Surgical secondary event requiring or resulting in**
Grade 1	Bedside care or oral medications
Grade 2	Intravenous medications, transfusion
Grade 3	Radiologic, endoscopic, or operative intervention required
Grade 4	Chronic disability or organ resection
Grade 5	Death
**BODY SYSTEMS**	
Cardiovascular system	Infection
Endocrine system	Metabolic
Gastrointestinal system	Musculoskeletal system
General	Nervous system
Genitourinary system	Pain
Head and neck	Pulmonary system
Hematologic or vascular	Wound or skin
system	

**Table 2 T2:** Classification of surgical complications according to Dindo–Clavien [(14) #398).

**Grade**	**Definition**
Grade I	Any deviation from the normal postoperative course without the need for pharmacological treatment or surgical, endoscopic, and radiological interventions. Allowed therapeutic regimens are: drugs as antiemetics, antipyretics, analgesics, diuretics, electrolytes, and physiotherapy. This grade also includes wound infections opened at the bedside
Grade II	Requiring pharmacological treatment with drugs other than such allowed for grade I complications. Blood transfusions and total parenteral nutrition are also included
Grade III	Requiring surgical, endoscopic, or radiological intervention
Grade IIIa	Intervention not under general anesthesia
Grade IIIb	Intervention under general anesthesia
Grade IV	Life-threatening complication (including CNS complications)^*^ requiring IC/ICU management
Grade IVa	Single organ dysfunction (including dialysis)
Grade IVb	Multiorgan dysfunction
Grade V	Death of a patient
Suffix “d”	If the patient suffers from a complication at the time of discharge, the suffix “d” (for “disability”) is added to the respective grade of complication. This label indicates the need for a follow-up to fully evaluate the complication

* *Brain hemorrhage, ischemic stroke, subarachnoidal bleeding, but excluding transient ischemic attacks*.

*CNS, central nervous system; IC, intermediate care; ICU, intensive care unit*.

### Patients and Inclusion and Exclusion Criteria

All adult patients (≥18 years of age), who are candidates for PD or DP and/or splenectomy. Exclusion criteria are as follows:

Patients with neoadjuvant radiation therapy with or without neoadjuvant chemotherapy within 4 weeks before surgery, pregnancy, and breastfeeding.Patients who were included in another clinical trial with an investigational treatment 1 month before inclusion are not included.Patients who have a personal medical history that may compromise the conduct, the evaluation, and/or the results of the trial according to the investigator are not included either.Allergy or hypersensitivity to somatostatin or somatostatin analogs or any component of the somatostatin or octreotide LAR or subcutaneous formulations.A previous treatment with somatostatin or somatostatin analogs or other components of the somatostatin or octreotide LAR or subcutaneous formulations.A current treatment by cyclosporine.No health insurance or social security.Non-compliance to medical treatment and/or analysis or patients potentially undependable or impossibility for the patients to complete the entire story.Patient under curatelle, tutelle, or in jail.

### Study Design and Setting

PreFiPS is a randomized, prospective multicenter study that aims to compare two different strategies to prevent pancreatic fistula after pancreatic surgery. The study design is deliberately based on the published randomized, double-blind, placebo-controlled phase III trial of Allen et al. [(13) #1171] to be able to compare the results in the two trials. Overall, 16 French high-volume pancreatic surgery centers (hospitals) will participate in the present study. On average, they each perform between 3 and 12 pancreatic procedures a week, and we expect that about half of them will be included in the present study. The inclusion visit will be done in the month before surgery in the department of surgery. The investigator checks for inclusion and non-inclusion criteria. The study will be presented to the patient. Before enrollment, the patient will be told about all potential risks and benefits associated with the study. Informed consent will be obtained from the subject before participation in the study. Pancreatic CT scan or MRI, within 6 weeks of surgery, will assess the main pancreatic duct dilatation, defined as main-duct diameter of >4 mm at the site of pancreatic transection on preoperative imaging. The following laboratory tests associated with care will be obtained within 14 days before therapy: complete blood count with white blood cell differential and platelet counts; albumin; prealbumin, ionogram, renal function, C-reactive protein, and liver enzymes; serum pregnancy test for women of childbearing potential before therapy. Follow-up visits will take place at 1, 3, 5, 7 (=postoperative days), and 45 days after surgery. End of research visit will take place at 90 days after surgery (±10 days). The length of participation will be 4 months, whereas the length of recruitment will be 42 months. Overall, the total length of the study will be 46 months.

### Experimental Plan

This is a French comparative multicentric phase III randomized controlled open trial comparing two groups receiving either somatostatin vs. octreotide of patients undergoing PD or DP with or without splenectomy. The study is controlled against octreotide, the gold-standard treatment for the prevention of postoperative PF. The research methodology is deliberately based on the SOM230 previous publication in the NEJM14, to be able to compare the different results [(13) #1171]. In the experimental regimen group, all patients will receive continuous intravenous infusion of somatostatin-14, 6 mg per day during 6.5 days starting just after skin incision and surgical exploration. In the conventional therapeutic strategy group, all patients will receive conventional prophylaxis arm: subcutaneous octreotide 100 μg 3 times a day for 6.5 days starting just after skin incision and surgical exploration (Figure 2). Amylase will be dosed on postoperative days 1, 3, 5, and 7, in the morning on the 24 h drain fluid and blood. Dosage of α-amylase is obtained with enzymatic colorimetric test, coloration intensity being proportional to the α-amylase activity. It is determined by measure of absorbance increase.

**Figure 2 F2:**
[figure not shown]
Experimental plan of PreFiPS study.

Patients with newly diagnosed pancreatic disease undergoing pancreatic surgery are screened for inclusion at the first surgical consultation. All patients fulfilling the inclusion criteria are asked to participate in the study. They are included in the study and sign the informed consent the day before surgery. Patients are 1:1 randomized in two arms, in the operating room just after skin incision and surgical exploration to exclude patients with carcinomatosis and metastasis. Surgical procedure is done according to each attending surgeon's preferences. Patients are seen in clinics 1 month after discharge and at 90 postoperative days. Table 3 resumes the chronology of the research.

**Table 3 T3:** Summary the chronology of the research.

**Actions**	**Inclusion visit**	**Surgery**	**Treatment**	**Postoperative days**	**Follow-up visit**	**End of research**
	**(D-1 month)**	**(D)**	**(during 6.5 days after surgery)(^a^)**	**1, 3, 5, 7**	**(D45 ± 7 days)**	**(D90 ± 10 days)**
Informed consent	(A day before surgery)					
History	X					
Clinical examination	X			X	X	X
Para-clinical examination	X				X	X
Amylase dosage in drain				X		
Tests (biochemistry, hematology, etc.)	X			X	X	X
Randomization		X				
Dispensation of treatment			X			
Compliance				X		
Adverse events				X	X	X
Postoperative quality recovery scale only in patients undergoing pancreaticoduodenectomy	(A day before surgery)			Only POD^b^7		

a *Glycemic controls will be done during treatment. Glycemic controls are routine care in patients candidate for pancreatic surgery*.

b *POD, postoperative day*.

### Randomization

Patients are 1:1 randomized in two groups, in the operating room just after skin incision and surgical exploration to exclude patients with carcinomatosis and metastasis, using permutated blocks of random size to stratify group assignment according to the type of procedure (PD or DP) and the presence or absence of main pancreatic duct dilatation (defined as main-duct diameter of >4 mm at the site of pancreatic transection on preoperative imaging). The randomization list is established centrally by the statistician of the URC et CIC Paris Descartes Necker Cochin before the start of the trial. The document describing the randomization specifications and the randomization list are kept confidentially in a secured place URC et CIC Paris Descartes Necker Cochin. The randomization list is implemented in a randomization tool of the e-CRF on Cleanweb software by the URC et CIC Paris Descartes Necker Cochin. Only the statistician and the person implementing the list in the e-CRF have access to the list during the trial. Randomization is performed by the site staff using the centralized tool in the e-CRF just after skin incision and surgical exploration to exclude patients with carcinomatosis and metastasis.

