### Sample Size Considerations

In daily surgical practice, pancreaticoduodenectomy represents about 80% of pancreatic resection. According to the last two randomized controlled studies performed in France within the FRENCH network, we can estimate the overall rate of grade B/C pancreatic fistula to be about 30% (Table 4). We hypothesize that the use of somatostatin can decrease this rate to 20%. To detect this difference, with an alpha risk of 5% and a power of 80%, a sample size of 294 eligible patients per arm is necessary. Assuming that approximately between 10 and 20% of the patients will not be resected for clinical reasons, a total of 654 patients should be included. These 654 patients will constitute the primary analysis population.

**Table 4 T4:** Reported rate of pancreatic fistula in recent French studies.

		**Type of surgery**	***n***	**% fistula**	
				**A/B/C**	**B/C**
Pessaux et al. (4)	Randomized controlled trial	Pancreaticoduodenectomy	158	34.2	30.3
Sa Cunha et al. (5)	Randomized controlled trial	Distal pancreatectomy	270	55.6	27.3

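### Randomisation in the operating room depends on absence of carcinomatosis and metastasis, not on PD or DP going ahead, so unresected patients can be randomised and dilute the primary analysis

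*Protocol article*

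**What the plan says.** All points are in the protocol article.

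- **Patients and Inclusion and Exclusion Criteria** admits adults "who are candidates for PD or DP and/or splenectomy". The exclusions begin with "Patients with neoadjuvant radiation therapy with or without neoadjuvant chemotherapy within 4 weeks before surgery, pregnancy, and breastfeeding" and go on to other trials, medical history, allergy, previous somatostatin or analogues, cyclosporine, insurance, compliance and legal status. Carcinomatosis, metastasis and unresectability are not among them.
- **Experimental Plan** (text after Figure 2) says of patients: "They are included in the study and sign the informed consent the day before surgery". Randomisation follows during the operation.
- **Randomization** sets the moment as "just after skin incision and surgical exploration to exclude patients with carcinomatosis and metastasis", stratified by procedure (PD or DP) and by duct dilatation.
- **Experimental Plan** has both study treatments "starting just after skin incision and surgical exploration", which is the same moment as randomisation, and describes the compared groups as patients undergoing PD or DP.
- **Sample Size Considerations** takes 294 eligible patients per arm and continues: "Assuming that approximately between 10 and 20% of the patients will not be resected for clinical reasons". It sets the total at 654 and declares all 654 to be the primary analysis population. **Statistical Analysis** specifies intention to treat for the primary endpoint.

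**The concern.** The primary endpoint is a fistula of the pancreatic anastomosis or of the closed remnant, so only a patient who has a PD or DP can have it. The main question, the treatment groups and one of the two stratification factors rest on the same condition. The operating-room gate tests something else, namely tumour spread. The two overlap, because many explored patients who are not resected will have metastasis or carcinomatosis, but they are not the same. Local unresectability or a change of procedure meets neither named exclusion.

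Read literally, such a patient is randomised into a PD or DP stratum that does not apply, starts study drug with no pancreatic transection, and enters the intention-to-treat analysis as a near-certain non-event. This blurs the population, shrinks the absolute difference between arms, and exposes patients to treatment for a complication they cannot have.

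The sample size section does not settle the matter. It foresees non-resection but does not say whether those patients leave before or after randomisation.

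**Working it through.** **1. Wording, side by side.**

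| Section | Condition used |
|---|---|
| Eligibility list | candidate for PD or DP; nothing on spread or resectability |
| Text after Figure 2, and Randomization | no carcinomatosis or metastasis at exploration |
| Experimental Plan | undergoing PD or DP |
| Sample Size Considerations | resected or not resected |

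The conditions differ, and none of the sections ties randomisation to confirmation of PD or DP.

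**2. The plan's own figures.** Inputs: 30% with octreotide, 20% with somatostatin, two-sided alpha 5%, power 80%, allocation 1:1. With pooled variance under the null and no continuity correction:

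n = [1.96·√(2·0.25·0.75) + 0.8416·√(0.3·0.7 + 0.2·0.8)]² / 0.10² = (1.2002 + 0.5119)² / 0.01 ≈ 293.2, that is 294 per arm, as stated.

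Inflation: 588 / 0.90 = 653.3, that is 654, as stated. At 20% it would be 588 / 0.80 = 735, so 654 covers only the lower end of the quoted range.

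**3. Unresected patients randomised and kept in the analysis.** Assumptions: a share u of the 654 is unresected, equally in both arms; these patients have no fistula; the resected have 30% and 20%. The rates become 0.30(1−u) and 0.20(1−u), with n = 327 per arm. Power is Φ{[δ√n − 1.96·√(2p̄(1−p̄))] / √(p₁(1−p₁) + p₂(1−p₂))}, where δ = p₁ − p₂ and p̄ is the mean of p₁ and p₂.

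For u = 10%: δ = 0.09 and p̄ = 0.225, so (0.09·18.083 − 1.96·0.5906) / 0.5871 = 0.80 and power is 78.8%.

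| u | Rates | Power with 654 | Total for 80% power |
|---|---|---|---|
| 0% | 30.0% v 20.0% | 84.1% | 588 |
| 5% | 28.5% v 19.0% | 81.6% | 628 |
| 10% | 27.0% v 18.0% | 78.8% | 674 |
| 15% | 25.5% v 17.0% | 75.8% | 726 |
| 20% | 24.0% v 16.0% | 72.6% | 784 |

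Dividing by 1−u restores the number of resected patients. That suffices if the unresected are left out of the analysis, but not if they stay in it: at 10% the total needed is 674, not 654.

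**4. Unresected patients removed before randomisation.** If 654 are consented, 654 × 0.90 ≈ 588 are randomised at 10% (power about 80%) and 654 × 0.80 ≈ 523 at 20% (power 75.4%). The 654 then cannot be the analysed population.

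**The case against.** The eligibility list and the operating-room check can be read as two successive steps. Eligibility is checked at a visit in the month before surgery, and occult spread can be seen only at exploration. A patient who turns out not to be having PD or DP is arguably no longer a candidate. The randomisation tool must be given the procedure as a stratum, which acts as an implicit check. In practice most surgeons would probably not randomise a patient they are about to close. Because patients are included the day before surgery, the expected 10 to 20% may be the very patients removed at exploration.

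Much of this stands. It shows that randomisation of unresectable patients is possible under the wording rather than certain. It does not remove the gap. A stratum can be filled in from the planned operation. The named reason for the gate is still spread alone. And reading the 10 to 20% as removed beforehand contradicts the statement that all 654 are analysed.

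A reader might infer more: that the gate misclassifies in both directions, because it also removes patients with metastasis who would still be resected, and that sites will treat these patients differently. The documents do not support this. They never say such resections occur. Excluding these patients before allocation is a legitimate choice of population that cannot bias the comparison between arms, and the instruction to exclude them is the same for every site.

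**Conclusion.** The point holds as a mismatch between the gate and what the trial studies, left unresolved by the sample size section. The intraoperative exclusion is absent from the eligibility list, and the condition that matters, PD or DP going ahead, is not required anywhere for randomisation.

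The effect on power depends on how many unresected patients are randomised. With all 654 analysed, it is under 2 points below target at 10% and about 7 points below at 20%; at 5%, power stays above 80%. This assumes equal shares in the two arms, no fistula in unresected patients, and 30% and 20% among the resected. A count of affected patients would need a split of non-resection by reason, which the documents do not give, so none is offered. Between-arm bias is not the issue: whoever the gate removes leaves before allocation. What is at stake is the definition of the population, dilution, and treatment of patients not at risk of the endpoint.

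**What to change.** 1. In the eligibility section, the text after Figure 2 and the Randomization section, state that after exploration the surgeon confirms PD or DP is going ahead, and that only then is the patient randomised. Record the confirmation together with the procedure stratum on the e-CRF randomisation form.
2. If carcinomatosis and metastasis remain exclusions in their own right, list them with the other exclusion criteria.
3. In Sample Size Considerations, say whether 654 counts consented or randomised patients, and align the sentence on the primary analysis population with that.

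The first two items need a wording amendment and one e-CRF field at a step that already exists; the time at which treatment starts is unchanged. The cost is in numbers: if 654 is a consent target, it must rise to keep 80% power when non-resection exceeds 10% (735 at 20%). Patients whose operative plan changes after randomisation will still be in the trial and in the intention-to-treat analysis, so some dilution remains.
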